**Study Summary**

| Study title | Impact of selective cyclooxygenase-2 inhibitor, celecoxib on cortical excitability and electrophysiological property in brain of healthy volunteer: Randomized, double-blind, placebo-controlled study |
| --- | --- |
| Principal investigator | [name], Department of Neurology |
| Financial support | Pfizer Inc. |
| Objective | To evaluate the impact of celecoxib on cortical excitability and electrophysiological properties of the brain in healthy humans by electroencephalography (EEG) and transmagnetic stimulation (TMS), as ample evidence based on animal models of epilepsy has demonstrated that celecoxib has anticonvulsant effects.  [Study 1]  1) Primary object  - To evaluate the change of cortical excitability and electrophysiological properties in brain cortex to single oral dose of celecoxib (400mg once) in healthy volunteer  - To evaluate the change of cortical excitability and electrophysiological properties in brain cortex by long-term treatment of celecoxib (200mg twice-daily for 7 days) in healthy volunteer  2) Secondary object  - To investigate the electroencephalographic changes by celecoxib in different locations and different frequency band.)  [Study 2]  1) To evaluate the change of cortical excitability and electrophysiological properties in brain cortex by long-term treatment of celecoxib (200mg twice-daily for 7 days) in healthy volunteer |
| Study design | Phase 1, randomized, placebo-controlled, double-blind study |
| Study period | Date of IRB approval ~ 2017.9.30. |
| Study subjects | Inclusion criteria  1. Healthy male or female aged between 20 and 50 years.  2. Body mass index between 16.0 and 30.0 kg/m^2^.  Exclusion criteria  1. History of cardiovascular disease (heart disease, stroke)  2. History of hepatic disease  3. History of gastrointestinal hemorrhage or inflammatory bowel disease  4. History of seizure (epilepsy)  5. History of any kind of medication within 1 week before screening  6. History of hypersensitivity to any medication  7. Females who were pregnant, breastfeeding, or intended to become pregnant  8. Presence of clinically significant electrocardiogram abnormality at screening  9. Aspartate aminotransferase (AST) or alanine aminotransferase (ALT) greater than 2.0 × the upper normal limit  10. Serum creatinine levels greater than 1.5 × the upper normal limit  11. Hyperkelamia, K level ≥ 5.5 mmol/L  12. Galactose intolerance |
| Number of study subject | A total of 40 subjects  Study 1 (EEG study) - Celecoxib: 10 subjects/ placebo: 10 subjects  Study 2 (TMS study) - Celecoxib: 10 subjects/ placebo: 10 subjects |
| Vulnerable subjects | Employees |
| Study methods | Celecoxib  - Dose: 400mg/day  - Route of administration: oral  - Duration of administration: 7 days  Study 1  - After randomization, EEG will be performed at baseline just before celecoxib (400 mg) or placebo delivery at 9 AM. EEG will be repeated 4 hours after the administration. The subjects will take celecoxib or placebo 200 mg twice a day for 7 subsequent days, and a third EEG will be conducted 4 hours after the final dose.  Study 2  - After randomization, TMS will be performed at baseline just before celecoxib or placebo (200 mg) delivery. The subjects will take 200 mg of celecoxib or placebo twice a day for 7 days. The second TMS recording will be performed 4 hours after the final dose. |
| Efficacy evaluation | Study 1  Primary end point  - Change of power spectra by single high dose of celecoxib.  Secondary end point  - Change of power spectra by 7-day treatment.  - Change of electroencephalographic properties by celecoxib in specific locations or frequency band by single dose or 7-day treatment.  Study 2  Primary end point  - Change of resting motor potential, amplitude of MEP, cortical silent period, intracortical inhibition and intracortical facilitation by 7-day treatment of celecoxib |
| Adverse effect evaluation | Adverse effect or serious adverse effect  All the adverse events including status changes after enrollment will be recorded, regardless of causal relationship to study drug or examination.  The subjects will be observed directly for 30 minutes after taking study drug for immediate reactions. The subjects also will be observed during TMS procedure and until 30 min after examination. The subjects will be asked if they had any pain (by Visual analogue scale) immediately after TMS. The occurrence and severity of any adverse events by study drug or device during this visit will be recorded on the appropriate CRF |
| Expected result | The knowledge from this research will deepen our understanding about inflammation and neuronal activity and will be a basis of clinical study for utilizing celecoxib as an anticonvulsant in the future. |

In brain tissue, concentration of celecoxib reach to maximum after 2-4 hours of oral administration.

◎ In this study, the volunteers take celecixob for 7 days, which is broadly used and safety has been proven. EEG and TMS will be performed before and after administration of study drug or placebo, and the exams are also safe and broadly used in clinical setting. As the study protocol is simple and safe, the outcome might be derived rapidly.

**2) Hypothesis and objectives**

To evaluate the impact of celecoxib on cortical excitability and electrophysiological properties of the brain in healthy humans by electroencephalography (EEG) and transmagnetic stimulation (TMS), as ample evidence based on animal models of epilepsy has demonstrated that celecoxib has anticonvulsant effects.

◎ Primary object

- To evaluate the change of cortical excitability and electrophysiological properties in brain cortex to single oral dose of celecoxib (400mg once) in healthy volunteer

- To evaluate the change of cortical excitability and electrophysiological properties in brain cortex by long-term treatment of celecoxib (200mg twice-daily for 7 days) in healthy volunteer

◎ Secondary object

- To investigate the electroencephalographic changes by celecoxib in different locations and different frequency band.

1. **Study drug (generic name and brand name), dosing, dosage forms**

◎ Study drug

- Generic name: Celecoxib

- Brand name: Celebrex^®^

- Dosing and dosage forms: 200mg capsule

◎ Medical device

- EEG

Conventional EEG (10-20 system), (Grass-Telefactor, USA)

- Motor evoked potential (transcranial magnetic stimulation. TMS)

Magstim 200 devices (Magstim Co. Ltd., Dyfed, S. Wales, UK).

A figure-of-eight shaped magnetic stimulator (type 9925, maximal output 2.2 Tesla)

1. **Eligiblity criteria of subjects and sample size estimation**

**1) Inclusion criteria**

1. Healthy male or female aged between 20 and 50 years.

2. Body mass index between 16.0 and 30.0 kg/m^2^

**2) Exclusion criteria**

1. Healthy male or female aged between 20 and 50 years.

2. Body mass index between 16.0 and 30.0 kg/m2.

Exclusion criteria

1. History of cardiovascular disease (heart disease, stroke)

2. History of hepatic disease

3. History of gastrointestinal hemorrhage or inflammatory bowel disease

4. History of seizure (epilepsy)

5. History of any kind of medication within 1 week before screening

6. History of hypersensitivity to any medication

7. Females who were pregnant, breastfeeding, or intended to become pregnant

8. Presence of clinically significant electrocardiogram abnormality at screening

9. Aspartate aminotransferase (AST) or alanine aminotransferase (ALT) greater than 2.0 × the upper normal limit

10. Serum creatinine levels greater than 1.5 × the upper normal limit

11. Hyperkelamia, K level ≥ 5.5 mmol/L

12. Galactose intolerance

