**4) Method of recruitment of subjects**

◎ On the bulletin board of Seoul National University or Seoul National University Hospital

◎ Prints on newspapers

1. **Study methods**
2. **Detailed study methods**

After screening test through blood lab, the subject will be included and randomized to each group as Table 1 if they met inclusion and exclusion criteria and agree informed consent.

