**4) Items of observation and methods**

**Study**

◎ Epidemiologic data

- Age, date of birth, age

- Medication history

- Medical history

- Physical examination

◎ Laboratory data

- Blood lab: AST/ALT, serum creatinine, potassium

- EKG

**-** EEG

- According to the international 10-20 system for 15 miniutes

- EEG (power spectra analysis)

The EEG data will be bandpass filtered (0.5-50 Hz) after re-referenced to the common average reference for analysis, and 10 epochs of 1.5 seconds in duration in the eyes-closed state without artefacts will be chosen. For power spectral analysis, the electrodes will grouped into frontal, central and parietal regions and analyzed by band width.

| Primary end point  - Change of power spectra by single high dose of celecoxib.  Secondary end point  - Change of power spectra by 7-day treatment.  - Change of electroencephalographic properties by celecoxib in specific locations or frequency band by single dose or 7-day treatment. |
| --- |

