**◎ Definition of Serious AEs**

ICH (International Conference on Harmonization) defined serious AE as below:

- resulted in death or is life-threatening,

- required inpatient hospitalization or prolongation of existing hospitalization,

- resulted in persistent or significant disability/incapacity,

- resulted in a congenital anomaly/birth defect.

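### Pregnancy is an exclusion, but neither the listed screening tests nor the visit tables include a pregnancy test

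*Protocol*

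**What the plan says.** The Inclusion criteria in section 10 of the protocol open both studies to women of childbearing age: "Healthy male or female aged between 20 and 50 years". Exclusion 7 in the same section, repeated in the Study Summary, bars "Females who were pregnant, breastfeeding, or intended to become pregnant".

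Section 11, Items of observation and methods, itemises the laboratory work separately for Study 1 and Study 2, in the same words: "Blood lab: AST/ALT, serum creatinine, potassium", with an EKG. The two visit tables at the end of that section tick consent, age, medication history, medical history, physical examination, blood lab and EKG at screening. Visit 2 has only drug administration, adverse events and the EEG or MEP recording. Neither table has a row for a pregnancy test at any visit.

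Section 11, Detailed study methods, makes the blood work the gate to randomisation: "After screening test through blood lab, the subject will be included and randomized to each group as Table 1", subject to the eligibility criteria and consent. No maximum interval between screening and Visit 2 is given.

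Exclusion 5 reads "History of any kind of medication within 1 week before screening". It makes no exception for any drug class, and the text does not mention contraception.

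**The concern.** The protocol treats pregnancy as a reason not to enrol a healthy volunteer, but schedules nothing that would find a pregnancy the volunteer does not know about. History identifies a known pregnancy. Neither history nor a routine physical examination can be relied on to identify an early, unrecognised one. A woman in that position meets every criterion as far as the scheduled procedures can show, passes the blood-lab gate and is randomised. If allocated to celecoxib, she takes it for about a week.

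What is at stake is subject safety and whether an eligibility rule can be applied as stated. The endpoints, the sample size and the analysis are not affected. The Expected result entry in the Study Summary describes gains in knowledge and names no therapeutic benefit to the volunteers, so the protection promised by an exclusion should be one that the procedures can deliver.

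**Working it through.** The plan states no figure on this point, so the main check is to set the exclusions beside the listed procedures.

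| Exclusion | Condition | Listed procedure that verifies it |
| --- | --- | --- |
| 8 | EKG abnormality | EKG at screening |
| 9 | Raised AST or ALT | AST/ALT in the blood lab |
| 10 | Raised creatinine | Serum creatinine in the blood lab |
| 11 | High potassium | Potassium in the blood lab |
| 7 | Pregnancy | None; history and physical examination only |
| 1 to 6, 12 | Past history, medication, intolerance | History |

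Exclusions 1 to 6 and 12, and the breastfeeding and intention parts of exclusion 7, are naturally settled by asking. Current pregnancy is different: like the conditions in exclusions 8 to 11, it is a present state that a simple test can establish.

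**Is it picked up later?** Medical history is ticked at screening and again at Visit 3, but not at Visit 2. Physical examination and blood lab are ticked at screening only. So nothing between screening and the first dose revisits pregnancy status, and by Visit 3 dosing is almost complete.

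**Illustration of size.** Two inputs are assumptions, not protocol figures: 20 of the 40 subjects are women, and a proportion p of 0.2% to 1% of them have an unrecognised pregnancy when dosing starts. The 1:1 allocation comes from Table 1 (20 celecoxib, 20 placebo over both studies).

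At least one such woman enrolled, either arm: 1 − (1 − p)^20
- p = 0.002: 1 − 0.998^20 = 0.039
- p = 0.005: 1 − 0.995^20 = 0.095
- p = 0.01: 1 − 0.99^20 = 0.182

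At least one such woman exposed to celecoxib, with probability p/2 per woman: 1 − (1 − p/2)^20
- p = 0.002: 1 − 0.999^20 = 0.020
- p = 0.01: 1 − 0.995^20 = 0.095

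The range is therefore about 4% to 18% for enrolment in either arm and about 2% to 10% for exposure to celecoxib.

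**The case against.** The strongest reply is that absence from the lists proves little, because the lists are incomplete in other respects. Pain on a visual analogue scale is required after TMS but appears in neither the Study 2 item list nor its visit table. Intracortical inhibition and facilitation are primary endpoints with no measurement described. Body mass index is a criterion, but no height or weight item is listed. The protocol never says that these are the only tests. Some front pages, the consent pages and the figures were not available to this review, so a test mentioned only there cannot be ruled out. The Dropout criteria also allow withdrawal of a subject found ineligible after enrolment.

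Part of this stands: the omission may be one of drafting. But sites work from the itemised tests and the visit tables, and both omit it in both studies. The dropout rule helps only if some procedure reveals the ineligibility, and none is scheduled that would.

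Three stronger readings are tempting, and the text does not support them.

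- A reader might infer that exclusion 5 selects women who use no contraception and so raises the risk. Read literally, it would keep out users of oral contraceptives, but the protocol never names them, and non-drug methods are compatible with it. The gap exists without exclusion 5.
- A reader might take the serious-event item "resulted in a congenital anomaly/birth defect" as evidence that the trial expects fetal harm. It is part of a generic ICH definition, and the protocol says nothing about fetal risk from an exposure of this length.
- A reader might take 4% to 18% as the chance of exposing a pregnancy to celecoxib. That range counts placebo subjects too; on the same assumptions the celecoxib figure is about half.

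**Conclusion.** The point holds as a mismatch between exclusion 7 and the listed screening procedures. Followed as written, the protocol could randomise a woman with an unrecognised early pregnancy and, under 1:1 allocation, expose her to celecoxib. It does not follow that this will happen: such a pregnancy must occur, and it must pass history and examination.

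The illustrative chance of about 2% to 10% for celecoxib exposure rests wholly on an assumed 20 women and an assumed prevalence of 0.2% to 1%, and would change in step with either. The finding does not depend on it. It rests on the test lists and the two visit tables. The sponsor should make the change, because it closes a real gap in subject protection at very little cost.

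**What to change.** Reconcile exclusion 7 with the test lists and visit tables. Add a pregnancy test for women of childbearing potential to the laboratory items of both studies, either as hCG on the blood sample already drawn at Visit 1 or as a urine test at Visit 2 before the first dose, and add a row for it to both tables. The Visit 1 option needs no new sample. The Visit 2 option also covers the unspecified interval since screening; if it is chosen, the result should be known before randomisation, so that a positive test does not remove one of only 10 subjects from a group.

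Separately, the sponsor should state whether exclusion 5 is meant to cover hormonal contraceptives. This review proposes no contraception rule.

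The cost is one inexpensive assay per woman and a few lines of protocol text. No extra visit or staff is needed, and neither the planned sample size nor the analysis changes.

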**3) Sample size estimation**

◎ Dose (200mg or 400mg) justification: In the previous study, the CSF concentration of celecoxib (200 mg) 4 hours after oral administration was 2 ng/ml (= 5 nM), and the Ki was 3.7 nM. As the tissue concentration peaks at 4 hours, 200 mg of celecoxib is sufficient to evaluate its effects. However, most subjects in the study are Caucasian, and genetic polymorphism of CYP2C9 varies from other racial and ethnic populations. In addition, the Ki value could not be directly applied to the electrophysiological study. Therefore, more doses of celecoxib are needed to evaluate the acute effect of celecoxib on EEG power spectra. In previous clinical trial of celecoxib with colorectal cancer patients, administration of 400 mg of celecoxib twice a day did not increased adverse effect compared to the administration of 200 mg of celecoxib twice a day. Therefore, single dose (400 mg) of celecoxib would be safe to healthy volunteers.

◎ No similar previous study has investigated the effect of celecoxib on brain activity. Based on a previous paper evaluating cortical excitability using the same method and a different drug (Joo, 2008), the mean difference was 0.4 and the standard deviation of each group was 0.4 and 0.2. The formula used to calculate the sample size was a two-sided paired or unpaired test. The significance level and power were set to 5%, and 0.8, respectively. Based on the calculation (OpenEPi (ver3)), n=10 in each group was appropriate for this study. Because this study has 4 groups, 40 subjects should be enrolled.

**4) Method of recruitment of subjects**

◎ On the bulletin board of Seoul National University or Seoul National University Hospital

◎ Prints on newspapers

1. **Study methods**
2. **Detailed study methods**

After screening test through blood lab, the subject will be included and randomized to each group as Table 1 if they met inclusion and exclusion criteria and agree informed consent.

**Table 1.**

| **Study 1** | **Study 2** |
| --- | --- |
| Celecoxib 1 group **(n = 10)** | Celecoxib 2 group **(n = 10)** |
| Placebo 1 group **(n = 10)** | Placebo 2 group **(n = 10)** |

**Study 1 (Figure)**

EEG will be performed at baseline just before celecoxib (400 mg) or placebo delivery at 9 AM, and EEG will be repeated at 1 PM, 4 hours after administration To evaluate the long-term effects of celecoxib, subjects will take celecoxib or placebo 200 mg twice a day for 7 subsequent days, and a third EEG will be conducted at 1 PM on the last day, 4 hours after the final dose

**
[figure not shown]
**

**Study 2 (Figure)**

TMS will be performed at baseline just before celecoxib or placebo (200 mg) delivery. The subjects will take 200 mg of celecoxib or placebo twice a day for 7 days. The second TMS recording will be performed 4 hours after the final dose

**
[figure not shown]
**

EEG: electroencephalography; TMS: transmagnetic stimulation

**2) Subject group and randomization**

This study is a double-blind, randomized placebo-controlled trial to reduced selection bias, allocation bias, balancing both known and unknown characteristics of the subjects, and maximize statistical power. The allocation assignment will be not opened during tue study to investigators and subjects. Online software (Research randomizer at https://www.randomizer.org) will generate randomization code and Pfizer Inc. will keep the Randomization Code/list in a secure manner. Blinding codes will be broken after completing all procedures of all targeted population. However, investigator might request the Log to be opened if s/he anticipates a real possibility of adverse events related to the investigational agents in urgent situation. Any request to break a randomization must be put into writing; the time, date, and reason of request must be documented with CRF

**3) Dose and route of administration of the study drug**

Study 1: celecoxib (400 mg) or placebo once on the first day, celecoxib or placebo 200 mg twice a day for 6 subsequent days and celecoxib or placebo 200 mg once on the last day, oral dministration

Study 2: celecoxib or placebo 200 mg twice a day for 7 days and celecoxib or placebo 200 mg once on the last day, oral dministration

**4) Items of observation and methods**

**Study**

◎ Epidemiologic data

- Age, date of birth, age

- Medication history

- Medical history

- Physical examination

◎ Laboratory data

- Blood lab: AST/ALT, serum creatinine, potassium

- EKG

**-** EEG

- According to the international 10-20 system for 15 miniutes

- EEG (power spectra analysis)

The EEG data will be bandpass filtered (0.5-50 Hz) after re-referenced to the common average reference for analysis, and 10 epochs of 1.5 seconds in duration in the eyes-closed state without artefacts will be chosen. For power spectral analysis, the electrodes will grouped into frontal, central and parietal regions and analyzed by band width.

| Primary end point  - Change of power spectra by single high dose of celecoxib.  Secondary end point  - Change of power spectra by 7-day treatment.  - Change of electroencephalographic properties by celecoxib in specific locations or frequency band by single dose or 7-day treatment. |
| --- |

**Study 2**

◎ Epidemiologic data

- Age, date of birth, age

- Medication history

- Medical history

- Physical examination

◎ Laboratory data

- Blood lab: AST/ALT, serum creatinine, potassium

- EKG

- Motor evoked potential (MEP)

- A figure-of-eight shaped magnetic stimulator will be located over the contralateral motor cortex to produce optimal motor potentials in the first dorsal interosseous muscle.

1) The resting motor threshold (RMT): the lowest intensity required to evoke MEPs in the FDI with a peak-to-peak amplitude of at least 50 μV in 4 of 8 trials

2) Peak-to-peak amplitude: With the FDI muscle in the relaxed state, stimuli will be delivered to evoke MEPs at stimulus intensities of 120%, 140%, and 150% (if possible) of RMT. [16]. Eight stimuli will be delivered randomly at each stimulus intensity every 5 seconds, and the average of the peak-to-peak amplitudes will be measured

3) Cortical silent period: The time between the end of the stimulus-induced MEP and the reoccurrence of voluntary EMG activity,

| Primary end point  - Change of resting motor potential, amplitude of MEP, cortical silent period, intracortical inhibition and intracortical facilitation by 7-day treatment of celecoxib |
| --- |

| **Study 1** | Screening  (Visit 1) | Visit 2(1^st^ day) | 2^nd^ day ~ 6^th^ day | Visit 3 (7^th^ day) |
| --- | --- | --- | --- | --- |
| Informed consent | V |  |  |  |
| Age, date of birth, age | V |  |  |  |
| Medication history | V |  |  |  |
| Medical history | V |  |  | V |
| Physical examination | V |  |  |  |
| Blood lab | V |  |  |  |
| EKG | V |  |  |  |
| Study drug administration |  | V | V | V |
| Adverse event |  | V |  | V |
| EEG |  | V (2 times) |  | V(once) |

| **Study 2** | Screening  (Visit 1) | Visit 2(1^st^ day) | 2^nd^ day ~ 6^th^ day | Visit 3 (7^th^ day) |
| --- | --- | --- | --- | --- |
| Informed consent | V |  |  |  |
| Age, date of birth, age | V |  |  |  |
| Medication history | V |  |  |  |
| Medical history | V |  |  | V |
| Physical examination | V |  |  |  |
| Blood lab | V |  |  |  |
| EKG | V |  |  |  |
| Study drug administration |  | V | V | V |
| Adverse event |  | V |  | V |
| MEP |  | V(once) |  | V(once) |

